### Procedures for collecting and handling data

All data will be entered into a password-protected Access database and each participant will be allocated a unique study number. Access to the password-protected database will be restricted to core University of Birmingham staff working on this study, who are trained in policies and procedures related to confidentiality. The University is registered under the data protection act and university policies and procedures related to confidentiality will be followed.

Demographic details will be provided by the GP for eligible people aged 50–69 years. Data on symptoms, risk factors and the acceptability of screening tests for colorectal cancer will be collected using the recruitment questionnaire. Participants will also complete a bowel preparation acceptability questionnaire prior to colonoscopy and two post-test (colonoscopy) acceptability questionnaires (prior to discharge at 10 days subsequent to colonoscopy). Blood sample results and colonoscopy findings will be communicated to the study team using the unique study number and linked to patient records.

### Justification of sample size

All types of colonic polyps have potential for malignant change but this is more common with increasing size, a villous growth pattern and more severe dysplasia [25]. Increasing age, adenoma size and a villous component have been associated with risk for high grade dysplasia [26].

In the USA, 11% (n = 329) of 3121 people aged 50–75 years without symptoms of lower gastrointestinal disease who had a complete colonoscopy had advanced colonic neoplasia (adenoma with a diameter of at least 10 mm, or villous features, high grade dysplasia, or invasive cancer) [27]. If large tubular adenomas were excluded, about 6% (n = 155) of people had lesions. About 32% (n = 105) of the 329 people only had lesions proximal to the rectum and sigmoid colon.

In Norway, 13% (n = 25) of 193 people aged 62–73 years who were offered a colonoscopy or flexible sigmoidoscopy and had a full colonoscopy had a high risk adenoma (adenoma greater than or equal to 10 mm and/or villous components and/or severe dysplasia) [28]. About 39% (n = 11) of the 28 high risk lesions were not in the rectum or sigmoid colon. In the UK, high risk lesions (greater than or equal to three adenomas, a polyp greater than 1 cm, tubulovillous or villous histology, severe dysplasia, malignancy, or greater than or equal to 20 hyperplastic polyps) were found in 5% (n = 1905) of 40674 people aged 55–64 years who were screened using flexible sigmoidoscopy [9]. This will not include proximal lesions that could be found on colonoscopy.

Any test that might usefully be employed to screen for malignant or premalignant colorectal lesions should have a high sensitivity to minimise the false negative rate. Based on our pilot data and conservatively assuming a community prevalence of 6% [9,27,28]. a sample of 700 people would be sufficient to estimate sensitivity within 3% (95% confidence) and specificity within 4% (95% confidence). If the community prevalence of high risk lesions is greater than 6%, our estimate of sensitivity will have greater precision.

Based on our pilot data (3.0% of the age group being suitable and consenting) and a practice list of 4500 with 18% of people aged 50–69 years [29]. 23100 people from 29 practices will be recruited to identify the 700 participants needed (Figure 1). The practices will be recruited via the Midlands GP Research Consortium (MidRec). This is a network of almost 400 research active practices with proven success in facilitating recruitment to primary care based trials. To maximise recruitment, the study has been designed to have minimal impact on general practices. Recruitment will be over 20 months.

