### Pilot work

We have completed a pilot study of 300 patients (all "urgent" referrals) attending a specialist colorectal clinic. In this high prevalence group (27% with pathology), the accuracy of serum MMP-9 for colorectal neoplasia was 73% (sensitivity 99%, specificity 63%, positive predictive value 50%, negative predictive value 99%). Serum MMP-9, therefore, appears to have the potential to be a useful screening test for colorectal neoplasia. There is a strong possibility, however, that our pilot was affected by spectrum bias. Although the sensitivity and specificity of a test are unaffected by disease prevalence, the performance of a diagnostic test can vary according to the spectrum of the population being tested, that is the severity and clinical presentation of the disease [19,20]. Evaluation of the accuracy and acceptability of serum MMP-9 in a primary care population, the target population for a potential screening test, is required to inform the utility of serum MMP-9 screening in the general population.

*Feasibility work *for this study has also been undertaken. One hundred and ninety eight questionnaires were distributed in December 2003. There was a return rate of 74% (n = 146), and 59% (n = 116) returned a completed questionnaire. Twenty four respondents (21% of 116) had symptoms other than only abdominal bloating and/or anal symptoms, and 13 of these people (54% of 24) agreed to take part in the study. Eleven, of the 13 agreeing to take part, were invited to a general practice research clinic, eight returned the availability slip and seven agreed to attend. Six of these people attended a research clinic and all were eligible and consented to have a blood sample and colonoscopy.

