### Methods of data analysis

#### Primary analysis

(1) ROC curve analysis will be undertaken to determine cut-off levels.

(2) Sensitivity, specificity, and positive and negative predictive values will be calculated with confidence intervals.

(3) The combination of MMP-9 level, symptoms, risk factors and socio-demographic status that best predict invasive and non-invasive colorectal neoplasia will be described.

(4) The acceptability of serum MMP-9 determination, FOB testing, flexible sigmoidoscopy and colonoscopy will be assessed by the initial questionnaire. The acceptability of serum MMP-9 determination and colonoscopy will also be assessed by a post-test acceptability questionnaire.

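### 700 people (about 42 cases) do not estimate sensitivity within 3%: at the pilot's 99%, exact 95% limits average a half-width of about 5 points and reach about 9 points below the estimate

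*Protocol article*

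**What the plan says.** In the protocol article, Justification of sample size states the planning basis as "Based on our pilot data and conservatively assuming a community prevalence of 6" per cent, and concludes that "a sample of 700 people would be sufficient to estimate sensitivity within 3% (95% confidence) and specificity within 4% (95% confidence"). It adds that a prevalence above 6% would improve the precision for sensitivity. It gives neither the expected number of cases nor the formula.

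The pilot values are in Pilot work: "sensitivity 99%, specificity 63%, positive predictive value 50%, negative predictive value 99" per cent. The same paragraph warns: "There is a strong possibility, however, that our pilot was affected by spectrum bias". The Discussion repeats that sensitivity and specificity can vary with disease spectrum.

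Primary analysis says only this about intervals: "Sensitivity, specificity, and positive and negative predictive values will be calculated with confidence intervals". No interval method is named.

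**The concern.** Sensitivity is estimated from cases alone, and 6% of 700 is 42. A 95% interval of ±3 points from 42 observations is possible only if the proportion is very close to 100%, and that is where the usual normal-approximation formula breaks down.

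Accuracy against colonoscopy is the first primary objective. The sample size section itself says that a useful screening test needs high sensitivity, to keep false negatives few. A reader who takes the ±3 at face value will expect the study to place sensitivity within about 96–100%. If the data can only place it between roughly 90% and 100%, the study has been presented as more decisive than its design allows on the property it treats as most important.

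**Working it through.** **Inputs.** N = 700, prevalence 6%, 95% confidence (Justification of sample size); sensitivity 99%, specificity 63% (Pilot work). Two-sided intervals (z = 1.96) are assumed. Derived: 700 × 0.06 = 42 cases and 658 non-cases.

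**1. Reproducing the plan's figures (normal approximation, Wald).**
- Sensitivity: 1.96 × √(0.99 × 0.01 / 42) = 0.0301, or 3.0 points. Inverted for exactly 3 points: 1.96² × 0.0099 / 0.03² = 42.3 cases; 42.3 / 0.06 ≈ 704 people.
- Specificity: 1.96 × √(0.63 × 0.37 / 658) = 0.0369, or 3.7 points, within the stated 4.

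Both figures reproduce, so the origin of the 3% is hardly in doubt.

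**2. Does the approximation hold for sensitivity?** Expected false negatives are 42 × 0.01 = 0.42. The formula's interval at 99% would run from 96.0% to 102.0%. The chance that all 42 cases test positive is 0.99^42 = 0.656, and the Wald interval then has zero width. Summed over Binomial(42, 0.99), the nominal 95% Wald interval covers 99% only 34% of the time.

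**3. What 42 cases give (exact, Clopper-Pearson).**

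| Cases detected | Exact 95% CI | Estimate minus lower limit | Half-width |
|---|---|---|---|
| 42/42 | 91.6–100% | 8.4 | 4.2 |
| 41/42 (97.6%) | 87.4–99.9% | 10.2 | 6.3 |

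For 42/42 the lower limit is 0.025^(1/42) = 0.916. Wilson lower limits are nearly the same: 91.6% and 87.7%.

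**4. Averages over Binomial(42, p), exact limits.** Each quantity is weighted by the probability of each possible count. The values below 99% are assumed, to show the range.

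| True sensitivity | Mean half-width | Mean distance to lower limit | Wald half-width |
|---|---|---|---|
| 99% | 5.0 | 9.1 | 3.0 |
| 95% | 7.6 | 11.2 | 6.6 |
| 90% | 9.9 | 13.0 | 9.1 |
| 80% | 12.7 | 15.0 | 12.1 |

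At 99%, Wilson gives a mean distance of 9.0 points and Jeffreys 6.7.

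**5. Separation from 90%.** 42/42 excludes 90% (lower limit 91.6%); 41/42 does not (87.4%). If true sensitivity is 99%, the chance of missing at least one case is 1 − 0.656 = 34%.

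**6. How many cases 3 points would take at 99%.** For the exact lower limit to lie within 3 points of the estimate: about 159 cases on average over the binomial counts (159 / 0.06 = 2,650 people), or 164–171 if the estimate is held at or near 99% (about 2,730–2,850 people). With Jeffreys limits the figure is about 120–127 cases (2,000–2,120 people). On the more lenient measure, a mean exact half-width of 3 points takes about 83 cases (83 / 0.06 ≈ 1,383 people). All exceed 700.

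**The case against.** **The arithmetic reproduces.** It does. The fault is not a slip in calculation but a formula used where it is invalid, and the precision it yields is still not what 42 cases give.

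**Lower-limit distance and half-width are different quantities.** This stands. Setting 9 points against ±3 and calling it three times worse compares a one-sided distance with a symmetric half-width. Like for like, 5.0 against 3.0 is about 1.7 times. Both measures should be reported. The lower limit is the one that matters for a claim of high sensitivity.

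**The 6% is conservative.** The article cites 11% and 13% from colonoscopy studies. At 77 cases (11%) the exact lower limit is 4.7 points below the estimate with none missed and 5.7 with one missed; at 91 cases (13%), 4.0 and 4.9. The corresponding half-widths are 2.3 and 3.5, then 2.0 and 3.0. So at the higher prevalences the half-width comes close to 3 or meets it, but the lower limit does not. The article makes its claim at 6%, and at 6% neither measure meets it.

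**Within 3% might mean the chance that the estimate falls within 3 points of the truth.** At a true 99% that chance is 93.4%. This is close to 95%, but it is not a confidence interval and it depends on the truth being 99%.

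**The study cannot tell 99% from 90%.** A reader might infer this, but it goes too far. In the likeliest outcome at 99% (42/42, probability 66%) the exact interval excludes 90%.

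**The reported interval would have 34% coverage.** A reader might infer this too. The article names no interval method, so nothing shows that Wald limits would be reported. The 34% shows only why Wald is a poor planning formula here. Leaving the method to an analysis plan is no fault.

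**Conclusion.** The statement that 700 people estimate sensitivity within 3% with 95% confidence is wrong as written. On the article's own inputs (42 cases, 99% sensitivity) the exact half-width averages about 5 points and the lower limit about 9 points below the estimate. Depending on count and method, the lower-limit distance runs from 8.4 to 10.2 points with Wilson or exact limits at 42/42 or 41/42, and averages about 7 with Jeffreys. Separation from 90% is probable but not assured.

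The 99% input is favourable. The article takes a cautious prevalence but plans at a pilot sensitivity that it suspects of spectrum bias, and at any lower sensitivity the interval widens, even by the plan's own formula. That bias is disclosed and is a stated reason for the study; the point is only that it does not carry through to the precision statement.

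A reader might also infer that the whole precision statement fails or that the study is too small to run. The documents do not support either: the specificity figure stands, and no hypothesis test or decision threshold depends on the 3%. The conclusion assumes two-sided 95% limits and exactly 42 cases; the actual number will vary.

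**What to change.** Keep 700 participants and leave the specificity figure unchanged. Replace the sensitivity figure with exact (or Wilson) limits for about 42 cases over a range of sensitivities. Possible wording: *With about 42 cases, the exact 95% confidence interval for sensitivity would be 91.6–100% if no case is missed and 87.4–99.9% if one is missed. At true sensitivities of 99, 95, 90 and 80%, the mean half-width is about 5, 8, 10 and 13 points, and the lower limit lies on average about 9, 11, 13 and 15 points below the estimate.* Wald half-widths should not be placed beside exact limits in the same statement.

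The cost is rewriting one sentence or short paragraph, with no change to recruitment, design or endpoints. The downside is that the stated sensitivity precision becomes visibly less favourable.

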### Methods of data analysis

#### Primary analysis

(1) ROC curve analysis will be undertaken to determine cut-off levels.

(2) Sensitivity, specificity, and positive and negative predictive values will be calculated with confidence intervals.

(3) The combination of MMP-9 level, symptoms, risk factors and socio-demographic status that best predict invasive and non-invasive colorectal neoplasia will be described.

(4) The acceptability of serum MMP-9 determination, FOB testing, flexible sigmoidoscopy and colonoscopy will be assessed by the initial questionnaire. The acceptability of serum MMP-9 determination and colonoscopy will also be assessed by a post-test acceptability questionnaire.

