#### Secondary analysis

Logistic regression analyses of appropriate subgroups (for example age or symptom profile) will be used to identify where an alternative cut-off may be more appropriate.

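### The MMP-9 cut-off is chosen by ROC analysis and, on the natural reading, assessed in the same cohort, so sensitivity will be optimistic by about 2 to 7.5 points depending on the selection rule

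*Protocol article*

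**What the plan says.** In the protocol article, Primary analysis, item (1) is "ROC curve analysis will be undertaken to determine cut-off levels". Item (2) is "Sensitivity, specificity, and positive and negative predictive values will be calculated with confidence intervals". No cut-off value is given, and the article describes one cohort of 700 with no hold-out or validation set. Secondary analysis adds logistic regressions in subgroups that "will be used to identify where an alternative cut-off may be more appropriate".

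Justification of sample size takes its planning values from the pilot and its prevalence from published studies, "conservatively assuming a community prevalence of 6" per cent. It concludes that "a sample of 700 people would be sufficient to estimate sensitivity within 3% (95% confidence) and specificity within 4% (95% confidence".

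Pilot work reports one operating point: "sensitivity 99%, specificity 63%, positive predictive value 50%, negative predictive value 99" per cent. The MMP-9 level behind it is not stated.

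**The concern.** A cut-off picked because it performs well in a set of cases partly fits the noise in those cases. Sensitivity read off at that cut-off in the same cases is then higher, on average, than it would be in new patients. With few cases the noise is large.

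Two parts of the article pull apart here. The precision calculation is for a proportion at a given threshold, but the primary analysis has the threshold still to be found. Sensitivity is also the measure that the sample-size section singles out as essential for a screening test, because it governs false negatives. An upward bias there makes the test look as if it misses fewer lesions than it does.

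**Working it through.** **Inputs.** N = 700 and prevalence 6% (Justification of sample size); pilot sensitivity 0.99 and specificity 0.63 in 300 patients, 27% with pathology (Pilot work). Derived: 0.06 × 700 = 42 cases and 658 non-cases.

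**1. The plan's own precision.** Half-width = 1.96 × √(p(1−p)/n).
- Sensitivity: 1.96 × √(0.99 × 0.01/42) = 3.01 points (stated: 3).
- Specificity: 1.96 × √(0.63 × 0.37/658) = 3.69 points (stated: 4).

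The stated figures reproduce as simple proportions, with nothing added for choosing the cut-off.

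**2. The pilot pair is a single operating point.** At 27% prevalence, PPV = 0.2673/(0.2673 + 0.2701) = 49.7%, NPV = 0.4599/(0.4599 + 0.0027) = 99.4%, and overall accuracy = 0.2673 + 0.4599 = 72.7%. These agree with the reported 50%, 99% and 73%, so some cut-off lay behind them.

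**3. Sensitivity-target rule: exact, whatever the marker's distribution.** Suppose the cut-off is the k-th smallest case value among n cases. Apparent sensitivity is 1 − (k−1)/n. Expected true sensitivity is 1 − k/(n+1). The optimism is the difference, (n+1−k)/(n(n+1)).
- Target 95%, n = 42: 40 of 42 must be positive, so k = 3. Apparent 40/42 = 95.2%, true 1 − 3/43 = 93.0%, optimism 2.2 points.
- Target 99%, n = 42: k = 1. Apparent 100%, true 1 − 1/43 = 97.7%, optimism 2.3 points.

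The cut-off depends only on the cases here, so specificity is unbiased.

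**4. Rules that trade sensitivity against specificity: simulation.** 6,000 replicates per scenario, 42 cases and 658 non-cases, marker N(μ,1) in cases and N(0,1) in non-cases. The article gives no distribution, AUC or rule, so these are assumptions. The pilot pair implies AUC = Φ((2.326 + 0.332)/√2) = 0.97 under this model; lower values show the range.

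| AUC | Youden: apparent / true sensitivity | Optimism, points | Wilson 95% coverage | Closest-to-corner: optimism, points | Wilson 95% coverage |
|---|---|---|---|---|---|
| 0.97 | 93.1 / 89.3% | 3.8 | 94% | 3.3 | 94% |
| 0.86 | 81.0 / 75.4% | 5.6 | 90% | 4.3 | 93% |
| 0.76 | 73.4 / 67.2% | 6.2 | 89% | 4.6 | 93% |
| 0.64 | 65.4 / 57.8% | 7.6 | 86% | 5.2 | 91% |

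A repeat simulation under Youden gave 4.0 points at AUC 0.97 and 7.5 at AUC 0.65, with coverage falling from 94% to 87%.

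In every scenario above, specificity optimism is at most 0.4 point and its coverage is about 95%. Under the 95% and 99% sensitivity targets, Wilson coverage for sensitivity is 95% to 98%.

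**5. Higher or lower prevalence.** The cited studies range from 5% to 13%, which is 35 to 91 cases. Going from 35 to 91 cases, Youden optimism falls from 4.4 to 2.2 points at AUC 0.97 and from 8.5 to 4.6 at AUC 0.64. For the 95% target, the formula in step 3 gives 34/(35 × 36) = 2.7 points at 35 cases and 87/(91 × 92) = 1.0 point at 91.

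**6. With the problem removed.** If the cut-off comes from an independent pilot-sized sample (81 cases, 219 non-cases), bias in both measures is at most 0.1 point, and Wilson coverage for sensitivity is about 95% to 96% at 42 cases.

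**The case against.** Four objections have force.

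- **The rule is not stated.** The article's emphasis on high sensitivity, and the pilot point of 99%/63%, suggest a sensitivity target rather than Youden; at AUC 0.97 the Youden point under the assumed model is about 91%/91%. The bias is then near 2 points and coverage is nominal. This stands, and is why the size must be given by rule.
- **The 3-point yardstick.** A reader might infer that the bias exceeds the planned precision. That is not like for like: the 3-point half-width belongs to a sensitivity of 99%. At the true Youden values of 89.3% and 57.8%, the half-width with 42 cases is 9.3 points (1.96 × √(0.893 × 0.107/42)) and 14.9 points (1.96 × √(0.578 × 0.422/42)), against optimism of 3.8 and 7.6. Near the planned operating point the comparison is 2.3 against 3.0.
- **The pilot cut-off is not printed.** Because the article itself suspects spectrum bias in the pilot, re-examining the threshold in primary care is legitimate. The stated aim is to evaluate accuracy in that population, so a locked pilot cut-off is not the only valid design.
- **Unseen detail.** The selection rule and any correction may sit in a full protocol or analysis plan, and the article does not say in words that the same data serve both steps.

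These points do not remove the core. One cohort is described, the ROC step is set in the future while the pilot is complete, and every same-data rule examined shifts sensitivity upward.

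**Conclusion.** The point holds for sensitivity. Followed as written, the primary analysis would overstate it by about 2 points under a sensitivity-target rule and by about 4 to 7.5 points under Youden (AUC 0.97 to 0.65). This rests on about 42 cases, on selection and evaluation in the same cohort and, for the Youden figures, on an equal-variance binormal marker. The article calls its 6% prevalence conservative; if prevalence is higher, the bias is smaller.

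A reader might go further and infer that specificity is also inflated, or that the intervals are too narrow in general. The documents do not support either. Specificity rests on about 658 non-cases and hardly moves. Undercoverage for sensitivity appears only under Youden-type selection, is slight at the pilot-implied AUC, and reaches 86% to 87% only at an AUC near 0.65, well below what the pilot implies. The remedy is a cheap improvement, not a reason to doubt the design.

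**What to change.** Before MMP-9 results are linked to colonoscopy findings, do one of the following:

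- Write a fixed cut-off into the protocol as the primary threshold, for example the one behind the pilot's 99%/63% if it is available. Report the ROC curve and AUC alongside, and label any cut-off re-derived in this cohort as secondary.
- Keep the ROC-derived cut-off as primary, name its selection rule, and report optimism-corrected sensitivity with bootstrap intervals that repeat the cut-off selection in every resample.

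Either takes about a paragraph, the second also a bootstrap, and neither needs more participants. The downsides are that a pilot cut-off may not be optimal in primary care, and that corrected sensitivity will look slightly less favourable. Timing matters: once the results are linked, a cleanly pre-specified threshold can no longer be set in this cohort.

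### The 700 participants are sized for sensitivity and specificity only, yet the primary analysis includes a search for the best predictor combination and the secondary analysis re-chooses cut-offs in subgroups; both would report substantially optimistic results

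*Protocol article*

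**What the plan says.** All references are to the protocol article.

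- **Primary analysis, item (3):** "The combination of MMP-9 level, symptoms, risk factors and socio-demographic status that best predict invasive and non-invasive colorectal neoplasia will be described". The abstract is firmer: it says that this combination is to be determined, for an outcome of invasive disease or polyps.
- **Secondary analysis:** "Logistic regression analyses of appropriate subgroups (for example age or symptom profile) will be used to identify where an alternative cut-off" would suit better. Age and symptom profile are given as examples; the number of subgroups is open.
- **Objective:** the primary objectives are the accuracy of MMP-9 against colonoscopy and its acceptability as a screening test. No primary objective concerns a combination of predictors.
- **Justification of sample size:** "a sample of 700 people would be sufficient to estimate sensitivity within 3% (95% confidence) and specificity within 4% (95% confidence"), based on the pilot and "conservatively assuming a community prevalence of 6"%. The section ties the 6% to a particular target: "If the community prevalence of high risk lesions is greater than 6%, our estimate of sensitivity will have greater precision". It gives no sizing for the combination or for subgroup cut-offs.

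**The concern.** An analysis that picks the best-predicting set from four domains, three of which are groups of variables, needs enough cases for the number of parameters tried. The study was sized for something else: one proportion among cases and one among non-cases. If the same few cases both select the combination and measure its performance, the reported discrimination is too high. The same applies, more sharply, to a cut-off chosen within a third of the cases. Regressions run separately by subgroup also do not test whether subgroups differ, so chance differences between their cut-offs can look like a reason for age- or symptom-specific thresholds.

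At stake is whether an apparent gain from adding symptoms to MMP-9, or from a subgroup threshold, can be believed. The protocol also sets out to assess referral guidelines and to establish MMP-9's screening potential, so such results would have an audience.

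**Working it through.** **1. Reproduce the plan's figure.** The pilot gives "sensitivity 99%, specificity 63%, positive predictive value 50%, negative predictive value 99"%. With z = 1.96, cases needed = z² × 0.99 × 0.01 / 0.03² = 42.3, and 42.3 / 0.06 = 704, in line with the stated 700. At N = 700:
- 42 cases: half-width for sensitivity 1.96 × √(0.99 × 0.01 / 42) = 3.0 points.
- 658 non-cases: half-width for specificity 1.96 × √(0.63 × 0.37 / 658) = 3.7 points.

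The 700 is therefore fully explained by these two precision targets.

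**2. Expected cases.**
- Assumed 6%: 700 × 0.06 = 42.
- US figure, "11% (n = 329) of 3121 people aged 50–75 years without symptoms of lower gastrointestinal disease": 700 × 0.11 = 77.
- Norwegian figure, 13%: 700 × 0.13 = 91.
- Pilot clinic, "In this high prevalence group (27% with pathology"), as an upper illustration only: 700 × 0.27 = 189.

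**3. How many parameters can 700 support?** The article gives no count, so 4, 10 and 20 are assumptions. For an expected shrinkage factor of S = 0.9, N = p / [(S − 1) × ln(1 − R²/S)]. At 6% prevalence the maximum R² is 0.365; R² is taken as 15% or 30% of it (assumed), that is 0.055 or 0.109.

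| Parameters | N, R² at 30% of maximum | N, R² at 15% of maximum | Cases per parameter (42 cases) |
|---|---|---|---|
| 4 | 308 | 638 | 10.5 |
| 10 | 771 | 1594 | 4.2 |
| 20 | 1542 | 3188 | 2.1 |

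The formula is linear in p, so 700 supports 700 × 4/638 = 4.4 to 700 × 4/308 = 9.1 parameters. At 11% prevalence 10 parameters need 549 to 1149, so 700 supports about 6 to 12.

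**4. Optimism of the fitted combination.** Simulated logistic models, n = 700: MMP-9 with AUC about 0.70, two weak real predictors, the rest noise (all assumed); performance in new data taken from 20,000 fresh subjects.

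| Cases | Parameters | Apparent AUC | AUC in new data | Difference | Calibration slope |
|---|---|---|---|---|---|
| 42 | 10 | 0.758 | 0.692 | 0.07 | 0.72 |
| 42 | 20 | 0.786 | 0.674 | 0.11 | 0.55 |
| 77 | 10 | 0.747 | 0.706 | 0.04 | 0.82 |
| 77 | 20 | 0.763 | 0.687 | 0.08 | 0.65 |
| 189 | 10 | 0.738 | 0.717 | 0.02 | 0.88 |
| 189 | 20 | 0.749 | 0.703 | 0.05 | 0.76 |

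A repeat with slightly different weak predictors gave differences of 0.06 and 0.12 at 42 cases, and 0.035 and 0.07 at 91. With 4 parameters and 42 cases it gave only 0.03. At 42 cases, going from 10 to 20 parameters raises the apparent AUC while the AUC in new data falls. If no predictor works at all, the apparent AUC is still 0.64 (10) or 0.69 (20) against a true 0.50.

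**5. Cut-offs re-chosen in subgroups.** Assumed: three equal subgroups with the same true cut-off, normal marker, AUC 0.70, Youden rule.
- 42 cases in all (14 cases and 219 non-cases each): apparent J 0.40, true J 0.26, overstated by 0.14. The highest and lowest of the three cut-offs lie about 0.8 marker SD apart on average, although none truly differs.
- 77 to 91 cases in all (26 to 30 each): apparent J about 0.37, true about 0.27, overstated by 0.10.
- At AUC 0.80 with 14 cases: 0.55 against 0.42.
- For reference, one common cut-off on 42 cases and 658 non-cases at AUC 0.70: 0.35 against 0.27.

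Even a perfect observed sensitivity has an exact 95% lower limit of 92% with 42/42 but 77% with 14/14.

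**The case against.** Several points count against a severe reading, and most of them stand in part.

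- **Silence on validation.** A reader might infer that no validation or optimism correction is planned. The article does not say so. The candidate list, selection rule and validation commonly sit in the full protocol or analysis plan, which are not shown. That silence is not part of this point.
- **The case count.** The 42 rests on a deliberately conservative prevalence of high risk lesions, whereas item (3) targets invasive and non-invasive neoplasia. The US 11% came from people without symptoms and this cohort has symptoms. More cases are therefore plausible. This stands and shrinks the optimism; it does not remove it at 77 to 91 cases.
- **The number of parameters is unknown.** With about four, 700 is adequate. This stands, but item (3) names three domains besides MMP-9, each holding several variables, so four would be a deliberate restriction. Backward elimination at 42 cases also gives smaller optimism: 0.74 against 0.70 (10 parameters) and 0.76 against 0.69 (20).
- **Modest wording.** The combination is to be described, and the subgroup work is secondary and tentatively phrased. True, but primary status and the aim of best prediction are not exploratory labels.
- **Subgroup method.** Separate fits without an interaction term are the natural reading of the text, not a stated fact. The number of subgroups and the Youden rule are assumptions; a plan that stresses sensitivity might use another rule.

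**Conclusion.** The point holds as a mismatch between the status of two analyses and the basis of the sample size. The article sizes the study for sensitivity and specificity, gives primary status to a predictor search that no primary objective calls for, and seeks alternative cut-offs from parts of an already small number of cases.

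Under the stated assumptions (10 to 20 parameters, MMP-9 AUC about 0.70), the AUC is overstated by about 0.07 to 0.12 at 42 cases and about 0.03 to 0.08 at 77 to 91. Re-chosen cut-offs in three subgroups overstate J by about 0.10 to 0.14 and differ spuriously.

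A reader might conclude that the results would be mostly over-fitted. The figures do not support that. At 42 cases the optimistic share of the apparent AUC above 0.50 is (0.758 − 0.692)/0.258 = 26% with 10 parameters and (0.786 − 0.674)/0.286 = 39% with 20. Substantially optimistic is the right description. The two accuracy precision targets are reproduced and are not in question here.

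**What to change.** - Move item (3) from primary to secondary and label it exploratory, in line with the stated objectives.
- Limit the candidate parameters to what the expected cases support, fixed before the data are seen. At 42 cases that is roughly 4 to 9 under the assumptions above. Which predictors, and which fitting method, is the sponsor's choice.
- Report bootstrap optimism-corrected discrimination and calibration, repeating any selection step inside the bootstrap.
- Replace the subgroup regressions by one model on all participants with MMP-9 × age and MMP-9 × symptom-group interaction terms. Report subgroup sensitivity and specificity, with confidence intervals, at the common cut-off. Label any subgroup-specific cut-off hypothesis-generating.

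No extra participants or data are needed. The cost is revised wording, some bootstrap programming, fewer predictors explored and less favourable reported performance.
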